## Abstract

**Background:**

Systemic inflammation in response to a femur fracture and the additional fixation is associated with inflammatory complications, such as acute respiratory distress syndrome and multiple organ dysfunction syndrome. The injury itself, but also the additional procedure of femoral fixation induces a release of pro-inflammatory cytokines such as interleukin-6. This results in an aggravation of the initial systemic inflammatory response, and can cause an increased risk for the development of inflammatory complications. Recent studies have shown that administration of the serum protein C1-esterase inhibitor can significantly reduce the release of circulating pro-inflammatory cytokines in response to acute systemic inflammation.

**Objective:**

Attenuation of the surgery-induced additional systemic inflammatory response by perioperative treatment with C1-esterase inhibitor of trauma patients with a femur fracture.

**Methods:**

The study is designed as a double-blind randomized placebo-controlled trial. Trauma patients with a femur fracture, Injury Severity Score ≥ 18 and age 18-80 years are included after obtaining informed consent. They are randomized for administration of 200 U/kg C1-esterase inhibitor intravenously or placebo (saline 0.9%) just before the start of the procedure of femoral fixation. The primary endpoint of the study is Δ interleukin-6, measured at t = 0, just before start of the femur fixation surgery and administration of C1-esterase inhibitor, and t = 6, 6 hours after administration of C1-esterase inhibitor and the femur fixation.

**Conclusion:**

This study intents to identify C1-esterase inhibitor as a safe and potent anti-inflammatory agent, that is capable of suppressing systemic inflammation in trauma patients. This might facilitate early total care procedures by lowering the risk of inflammation in response to the surgical intervention. This could result in increased functional outcomes and reduced health care related costs.

**Trial registration:**

clinicaltrials.gov NCT01275976 (January 12th 2011)

## Background

Trauma is a major cause of morbidity and mortality in people under the age of 50 years in the western world [1]. Death can occur as a direct result of the trauma induced injury, or as result of a dysfunctional immune response [2]. This excessive immune reaction is caused by the response to tissue injury, such as seen after trauma, surgery or burns. An overwhelming innate immune response is considered to be a major risk factor in the development of post-traumatic organ failure and sepsis. Additional injury, induced by surgical intervention, can increase the overall immune inflammatory reaction [3].

The lung is most often the first organ to be affected by an exaggerated systemic immune response, which can result in an acute respiratory distress syndrome (ARDS). This functional impairment can be followed by other organs, such as the liver, gastrointestinal tract and kidneys, leading to the so-called multiple organ dysfunction syndrome (MODS). Presence of ARDS and MODS is a major risk factor for mortality, long time morbidity, a prolonged hospital stay and high health care costs [4].

One of the early and systemically released cytokines in the early inflammatory response, is the pro-inflammatory cytokine interleukin-6 (IL-6). Therefore, this cytokine is widely used as an indicator for severity of the systemic inflammatory response in clinical studies [5]. Serum IL-6 levels have been demonstrated to be closely related to the magnitude of the injury (burden of trauma/first hit) and to the operative procedure (second hit) [6,7]. There is a correlation between the IL-6 concentration and the underlying injury severity. Patients with a Injury Severity Score (ISS) > 18 showed a more pronounced rise of IL-6 concentration compared to patients with a lower injury severity [8].

Femur fractures, have been found associated with a profound systemic inflammatory response [9-11]. Ideally, fractures should be managed without a clinically important delay to prevent excess blood loss, and preserve function. However, in case of femur fractures, internal fixation increases systemic inflammation [12]. In trauma patients with an already activated inflammatory response, this increase greatly enhances the risk of an excessive immune response [13,14]. To address this problem, the concept of damage control orthopedics (DCO) was developed [15,16]. This concept aims at minimizing the surgically induced inflammatory response through limiting surgical procedures [16,17]. However, DCO is a controversial approach, because limiting surgical procedures, can lead to a reduced quality of fracture healing, multiple interventions and a prolonged hospital stay. This places the treating surgeon with a difficult dilemma: early total care versus damage control [18-20].

Therefore, there is an unmet need for limiting/preventing the surgical induced inflammation, other than limiting or delaying surgery. Until now, there is a lack of pharmacological interventions that can reduce this surgery induced inflammation.

A promising intervention to attenuate the systemic innate immune response is the treatment with a high concentration of C1-esterase inhibitor (C1-INH) [21]. C1-INH is an acute phase protein, produced by the liver in response to inflammatory conditions. C1-INH is a major inhibitor for both the complement and the contact system, and is, therefore, an important regulator of inflammatory reactions [22,23]. Apart from the modulation of the these systems, C1-INH has also been shown to attenuate systemic inflammation independently of the activation of complement [24]. In fact, Dorresteijn et al showed that administration of C1-INH, in a 'human endotoxemia model', attenuates the release of pro-inflammatory cytokines, including IL-6, in healthy male volunteers [21]. This model evokes a systemic inflammatory response in the absence of complement activation [21,25].

### Aim of the study

The aim of this study is to ascertain whether administration of C1-INH in trauma patients with a femur fracture can reduce the release of pro-inflammatory cytokines and, therefore, will contribute to attenuation of the inflammatory response, in response to a surgical intervention (second hit). This study can provide proof of principle for C1-INH as a potential drug for the prevention of late inflammatory complications in trauma patients.

## Methods

### Objectives

Attenuation of the surgery-induced additional systemic inflammatory response by perioperative treatment with C1-INH in trauma patients with a femur fracture. And the effect of C1-INH on clinical outcome (e.g. ARDS, MODS, mortality, length of hospital stay).

### Study design

This clinical trial is a double blind, placebo-controlled, randomized study, investigating the anti-inflammatory effect of C1-INH on systemic inflammation induced by fixation of the femur fracture in trauma patients.

This study is conducted in accordance with the principles of the Declaration of Helsinki [26] and Good Clinical Practice Guidelines [27]. The independent ethics committee of the University Medical Centre Utrecht (UMCU) approved the study. Written informed consent will be obtained from all participating patients.

### Study population

Seventy multi-trauma patients presented at the emergency department of the UMCU with an ISS ≥ 18 and a femur fracture which need fixation, will be included in the study. Patients are eligible for the study if they meet all the inclusion and none of the exclusion criteria (Table 1).

**Table 1 T1:** Patients in- and exclusion criteria

*Inclusion criteria*	*Exclusion criteria*
Multi-trauma patient ISS* ≥ 18 Femur fracture Age 18-80 years Informed consent	Congenital C1-inhibitor deficiency Use of immune suppressants Known hypersensitivity for blood Products Pregnancy Fixation of the femoral fracture with external fixation or osteosynthesis

*ISS = Injury Severity Score

### Randomization

Subjects are randomly allocated to either the C1-INH group (intervention-group) or the placebo-group just before the start of the surgical repair of the femur fracture, using an 1:1 allocation ratio. Randomization will be performed by the distributing pharmacy (UMCU, The Netherlands) with the use of Design version 2.0 (Systat Software Inc., Chicago, IL, USA). The C1-INH and placebo solutions are prepared in identical non-transparent infusion bags, ensuring the double-blind fashion of the study. Patients, treating surgeons, investigators and nursing personnel involved in the study will be unaware of the randomization, and therefore, the solution applied.

### Study protocol

When trauma patients meet the inclusion criteria, a first blood sample is taken within 12 hours after trauma. This blood sample serves as a reference for the degree of inflammation immediately after injury. Because the first blood sample needs to be drawn within 12 hours after trauma, it is possible that the first sample is drawn without the necessary informed consent and will be analyzed directly. This delayed informed consent may be required because the inflammatory response after the initial trauma is visible in the blood within the first 12 hours after trauma. Of course, the informed consent is obtained as soon as possible if the patient or his/her legal representative is able to. If no consent is obtained, the analyzed blood and the data will be destroyed and the patients will not receive C1-INH or placebo, because the randomization will only take place after informed consent is obtained.

Patients receive femur fixation surgery according to the current protocol in the UMCU. Just after induction of anesthesia a second blood sample will be drawn and after this withdrawal the subject receives either C1-INH in a dose of 200 U/kg body weight (n = 35) or placebo (saline 0.9%, n = 35) intravenously. Two hours and six hours after the skin incision for the surgical procedure for femoral fixation the next blood samples are taken. The last samples are taken 24 and 48 hours and seven days after procedure of femoral fixation. An overview of the time frame of the study is shown in Figure 1.

**Figure 1 F1:**
[figure not shown]
**Time frame**.

### Outcome measurements

The primary outcome will be the change in serum IL-6 concentration before and after surgical repair of a femur fracture in trauma patients in the presence or absence of C1-INH. We have chosen IL-6 as our primary endpoint because IL-6 is one of the earliest released pro-inflammatory cytokines after trauma, which is detectable by multiplex assays. Several clinical studies have shown that IL-6 is a good marker for the severity of inflammatory response [5,8,10]. Because not all patients are operated at the exact same time after trauma we will use the Δ IL-6 serum concentration (the difference in IL-6 level between t = 0, at the start of the operation, and t = 6, six hours after start of the operation) as our primary endpoint. This allows the detection of the difference between the systemic inflammation in patients treated with or without C1-INH.

Secondary biochemical outcomes include the production of various pro- and anti-inflammatory cytokines, cellular activation markers and complement. Various hematological variables and clinical chemistry measurements, such as haemoglobin, haematocrit, leukocyte count, platelet count, C-reactive protein and fibrinogen, are also determined. These values reflect the clinical condition of the patient and the severity of inflammation.

Secondary clinical outcomes include the effect of C1-INH on the presence or absence of ARDS or MODS and appearance of SIRS, sepsis or septic shock. To evaluate the presence of these clinical conditions the Systemic Response Syndrome (SIRS)-score [28] and the Sequential Organ Failure Assessment (SOFA)-score [29] will be calculated on a daily base during hospitalization of the study subjects. The duration of admission at the intensive care unit, duration of mechanical ventilation and total days of hospital admission are all recorded.

### Sample size calculation

The sample size calculation is based on damping of the increase in serum IL-6 concentration by 30% in the C1-INH group, compared to the placebo group [21,30,31]. With an expected standard deviation of 50% [30,31] and a relevant decrease of IL-6 concentration of 30% [21,30,31], 35 patients in each sample-group (C1-INH or placebo) are needed to find a statistically significant difference (power 80%, Type 1 error rate 0.05).

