### Interim analysis

In this study there will be two analyses performed, one interim and the final analysis, using the O'Brien Fleming method [33]. The alpha used for the interim analysis will be 0.0054, and for the final analysis the alpha used will be 0.0492.

The interim analysis will be conducted by an independent Data Safety Monitoring Board (DSMB) after the inclusion of 35 succeeding patients, The DSMB is composed of three independent members, of which two clinicians and one statistician. After the interim analysis the DSMB is able to make recommendations. In case of clear benefit, harm or futility of the treatment, the DSMB might decide to end the study early.

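### With a 30% effect and a 50% SD, 35 patients per arm give about 70% power in a two-sided 0.05 test, not the stated 80%

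*Protocol article*

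**What the plan says.** The Sample size calculation section of the protocol article gives every input: "With an expected standard deviation of 50% [30,31] and a relevant decrease of IL-6 concentration of 30"%, followed by the result, "35 patients in each sample-group (C1-INH or placebo) are needed to find a statistically significant difference (power 80%, Type 1 error rate 0.05"). It does not say whether the 0.05 is one-sided or two-sided.

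The Randomization section specifies allocation "using an 1:1 allocation ratio". The Statistical analysis section names a Student's t-test on the change in IL-6 as the primary analysis, sets the threshold at p < 0.05, and mentions no one-sided test.

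The Interim analysis section plans two looks by the O'Brien-Fleming method: "The alpha used for the interim analysis will be 0.0054, and for the final analysis the alpha used will be 0.0492". The interim look comes after 35 patients, and the monitoring board may end the trial for benefit, harm or futility.

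**The concern.** For a 30% difference against a 50% SD, a conventional two-sided 0.05 calculation gives a number in the mid-forties per arm. Thirty-five is about what a one-sided 0.05 calculation gives. If the trial is then judged by a two-sided rule, as the interim and final levels suggest, it does not have the power claimed for it.

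This concerns the primary endpoint of a trial meant to provide proof of principle. Readers of a non-significant result would take the risk of a false negative to be 20% when it is about 30%, half as large again. They could then give the result more weight against the drug than the design supports. The target of 70 is exactly 2 × 35, so the printed calculation leaves no margin for missing six-hour samples.

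**Working it through.** **Inputs.** Difference 30% and SD 50% (Sample size calculation); 35 per arm, 80% power, type 1 error 0.05 (same section); 1:1 allocation (Randomization); t-test on the change in IL-6 (Statistical analysis). Standardised effect d = 30/50 = 0.60.

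**Step 1: reproduce the plan's figure.** Normal approximation: n per arm = 2 × (z for alpha + z for power)² / d².

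- One-sided 0.05: 2 × (1.645 + 0.842)² / 0.36 = 34.3, rounded up to 35. The t-test version gives 35.04, and its power at 35 per arm is 79.96%.
- Two-sided 0.05: 2 × (1.960 + 0.842)² / 0.36 = 43.6, rounded up to 44. The t-test version gives 44.6, rounded up to 45.

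So 35 is the one-sided result. It is not a slip in the arithmetic.

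**Step 2: power at 35 per arm.** The noncentrality is 0.60 × √(35/2) = 2.51, with 68 degrees of freedom.

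| Test | Power, normal approximation | Power, t-test |
|---|---|---|
| One-sided 0.05 | 80.7% | 80.0% |
| Two-sided 0.05 | 70.9% | 69.7% |
| Two-sided 0.0492 (stated final level) | 70.6% | 69.4% |

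The early look does not recover the shortfall. With both looks at the stated levels and the interim at half the information, two-sided power is 70.9% by normal approximation and 69.8% by simulation of the t-test design (200,000 trials).

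**Step 3: which sidedness does the article's decision rule use?** With one look at half the information, O'Brien-Fleming critical values must stand in the ratio √2 = 1.4142.

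- Levels read as two-sided: 0.0054 gives z = 2.782 and 0.0492 gives z = 1.967. Ratio 1.4145.
- Levels read as one-sided: z = 2.549 and 1.653. Ratio 1.542.

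Only the two-sided reading has the O'Brien-Fleming shape. The exact levels point the same way: for an overall two-sided 0.05 they are 0.0052 and 0.0480, close to those stated, whereas for an overall one-sided 0.05 they are 0.0088 and 0.0467.

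**Step 4: what 35 per arm can detect.** Two-sided 0.05 with 80% power needs d = 0.68 by t-test, and 0.68 × 50% = 34%. By normal approximation the detectable difference is 2.80 × 50% × √(2/35) = 33.5%. Put the other way, a 30% difference would have 80% power only if the SD were about 45%.

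**The case against.** The strongest reply is that the authors intended a one-sided test. The aim is directional throughout (attenuation, damping, decrease), the sample size section does not say two-sided, and 35 matches the one-sided answer. A condensed article may also leave sidedness to the full protocol. Most of this can be granted: silence on sidedness alone would not be a finding, and a one-sided calculation is the likely origin of the number. It does not remove the problem. The levels in the Interim analysis section are two-sided in shape, and the article foresees stopping for harm as well as benefit. If the one-sided reading is adopted, the error moves to that section; the two sections cannot both stand as printed.

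A second reply is that the levels do not match an exact two-sided design either. That is true: 0.0054 and 0.0492 together spend about 0.0513 two-sided with the interim at half the information. The mismatch is small, and the ratio of critical values still identifies them as two-sided.

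A third reply concerns scale. If the SD were 50% of each arm's own mean (50 and 35), 33 per arm would suffice two-sided, with 83% power at 35. On a log scale with SD 0.5 the requirement is 31 (85% power at 35), and with a coefficient of variation of 0.5 it is 28 (88%). These readings would rescue the power claim. Each needs an assumption the article does not make, none returns 35, and none fits a single SD used with a t-test on the raw difference. The cited sources for the SD are not available here, so d = 0.60 remains the reading of the text as printed.

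**Conclusion.** The concern holds. On the article's own inputs, and with the two-sided testing that its interim and final levels imply, 35 per arm give 69.7% power at 0.05 and 69.4% at 0.0492, about ten points below the stated 80%. For 80%, 44 (normal approximation) or 45 (t-test) per arm are needed. The conclusion rests on two readings: that the 30% and the 50% are on the same scale with a common SD, so that d = 0.60, and that the primary test is two-sided. The first follows the wording and the planned t-test. The second is inferred from the O'Brien-Fleming levels and the provision for stopping for harm, since the article never states it. No allowance for losses is included in these figures; any loss would lower the power further.

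**What to change.** Declare in the Statistical analysis section that the primary test is two-sided, and correct the Sample size calculation section to match. The smallest change keeps 70 patients and replaces the power statement, for example: with 35 patients per arm, a two-sided t-test at the final significance level has about 70% power to detect a 30% reduction assuming an SD of 50%, and 80% power to detect a reduction of about 34%. The 30% should stay in the statement, because the article names it as the relevant effect. The section should also say on what scale the 50% SD is expressed. This costs one or two sentences and a less favourable power figure, with no extra patients.

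If the sponsor regards 80% power at 30% as essential, the alternative is about 45 per arm (90 in total) before any allowance for losses, which is 20 more patients. The Trial status section reports that nobody had been included, so on the article's account either change could be made before any data exist. If a one-sided test was truly intended, that must be declared and justified, and the interim and final levels rederived to agree with it.

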### Statistical analysis

The primary endpoint, the Δ IL-6, will be determined with the use of a Students' *t-test*. The occurrence of inflammatory complications, such as MODS and ARDS, will be examined with the use of a survival analysis, such as Kaplan Meier or Cox proportional Hazard [32].

For comparisons, a *t-test *or Mann Whitney U-test will be used as appropriate.

Changes over time will be analyzed using repeated measurement analysis with time as within factor and treatment as between factor, using Analysis of Variance.

A *p*-value < 0.05 is considered statistically significant.

The data will be analyzed using software programs SPSS version 17.0 (SPSS Inc., Chicago, IL, USA) and GraphPad Prism (GraphPad Software Inc., La Jolla, CA, USA).

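### The primary test, an unadjusted t-test on the raw change in IL-6, is valid but less efficient than a baseline-adjusted analysis of log IL-6

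*Protocol article*

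**What the plan says.** All three places are in the Methods of the protocol article.

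- **Outcome measurements** defines the primary endpoint as "the difference in IL-6 level between t = 0, at the start of the operation", and t = 6. It is a plain difference in concentration. The reason given for a change score is: "Because not all patients are operated at the exact same time after trauma we will use the Δ IL-6 serum concentration".
- **Statistical analysis** assigns one test to it: "The primary endpoint, the Δ IL-6, will be determined with the use of a Students" t-test. The choice between a t-test and a Mann-Whitney test stands in a separate sentence about unspecified comparisons. The repeated-measures ANOVA is for changes over time. Neither alters the primary test.
- **Sample size calculation** plans in percentages. It words the effect first as "damping of the increase in serum IL-6 concentration by 30% in the C1-INH group" and then as a "relevant decrease of IL-6 concentration of 30" per cent. The spread enters as "With an expected standard deviation of 50" per cent, with no statement of what it is a percentage of. The error rates are "power 80%, Type 1 error rate 0.05", with no statement of one-sided or two-sided testing.

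**The concern.** The t = 0 sample is a strong candidate covariate, and the plan uses it only by subtraction. That causes three difficulties.

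1. Subtraction imposes a slope of 1 on baseline. Unless the true slope happens to be 1, the change still depends on the starting level, and explainable variation stays in the error term.
2. The stated motive is that surgery takes place at different times after injury. Subtraction removes the level reached at the start of surgery. It does not remove the rise or fall over the next six hours that depends on where the patient is in the post-injury course, and no term in the analysis does so.
3. If IL-6 is right-skewed, with spread that grows with level, a few patients with very high values carry much of the variance of a raw difference.

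At stake is the precision of the only endpoint with a sample size calculation, in a trial of 70 patients.

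**Working it through.** **Inputs from the article.** Difference 30%, SD 50%, alpha 0.05, power 80%, 35 per arm, 1:1 allocation. Taken at face value, d = 30/50 = 0.6.

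**Inputs assumed, because the article does not give them.** Pre/post correlation r; the ratio k of the SD at t = 6 to the SD at t = 0; the shape and CV of IL-6; no dropout.

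**Step 1: the plan's own figure.** n per arm = 2(z_alpha + z_beta)² / d².
- One-sided: 2(1.645 + 0.842)² / 0.36 = 34.4, so 35. This matches the plan.
- Two-sided: 2(1.960 + 0.842)² / 0.36 = 43.6, so 44. This does not match.
- With 35 per arm, t-based power is 80.0% one-sided and 69.7% two-sided. The two-sided 70% is the reference below.

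**Step 2: change score against ANCOVA on the same scale.** With SD s at t = 0 and ks at t = 6:
- variance of the change = s²(1 + k² − 2rk)
- residual variance after ANCOVA = k²s²(1 − r²)
- ratio = k²(1 − r²) / (1 + k² − 2rk), which is (1 + r)/2 when k = 1
- power follows from an effective d of 0.6/√ratio, with 35 per arm, two-sided 0.05
- correlation of change with baseline = (rk − 1)/√(1 + k² − 2rk)

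| r | ratio, k = 1 | power, k = 1 | corr., k = 1 | ratio, k = 2 | power, k = 2 | corr., k = 2 |
|---|---|---|---|---|---|---|
| 0.3 | 0.65 | 87% | −0.59 | 0.96 | 71% | −0.21 |
| 0.5 | 0.75 | 82% | −0.50 | 1.00 | 70% | 0 |
| 0.7 | 0.85 | 77% | −0.39 | 0.93 | 73% | 0.27 |

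With equal variances the gain is 7 to 17 points. If the SD doubles, as it would in the placebo arm if IL-6 doubled with a constant CV, the gain is 0 to 3 points. At k = 2 and r = 0.5 the true slope rk is exactly 1, so the change score is already optimal.

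**Step 3: the scale.** Simulated log-normal IL-6, 35 per arm, placebo doubling, treated/placebo ratio 0.70 at t = 6, r = 0.5, two-sided 0.05:

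| CV | raw-change t-test | raw-scale ANCOVA | log-scale ANCOVA |
|---|---|---|---|
| 50% | 91% | 91% | 94% |
| 100% | 36% | 37% | 51% |
| 150% | 19% | 20% | 34% |

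Repeat runs differ by one or two points. Adjusting on the raw scale adds almost nothing here; the gain appears on moving to the log scale. The log scale still needs the estimated slope. In a companion simulation with log SD 0.5 and r = 0.5, power was 87% for the raw change, 84% for a t-test on log change and 92% for log ANCOVA. Under no treatment effect the raw-change t-test rejected in about 4–5% of trials, so its type I error holds.

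**Step 4: the planning effect.** The two wordings are not the same effect. Take baseline 100 and placebo 200 at t = 6. Damping the increase by 30% gives 170, a ratio of 0.85. Lowering the concentration by 30% gives 140, a ratio of 0.70. Step 3 uses the second reading.

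**The case against.** The strongest reply is that the named test is valid. Randomisation balances baseline IL-6 and time since trauma on average, and the simulated error rate is right, so this is a preference about efficiency. That stands, and it sets the limit of the point. Stronger readings that a reader might infer are not supported:

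- **That the result is biased, or that a baseline imbalance carries over in full.** Given an imbalance, the expected shift in the change contrast is (rk − 1) times it. With equal variances and r = 0.7 that is −30% of the imbalance; with k = 2 and r = 0.5 it is zero.
- **That the baseline is thrown away.** It is used, by subtraction.
- **That the test contradicts the planning figures.** If 30% and 50% are fractions of the mean placebo increase, they map directly onto a raw-change t-test with d = 0.6. What the article does show is two unequal wordings of the effect and an SD without a base.
- **That the article claims to correct for time since trauma.** It gives varying time to surgery as its reason for using the change, and goes no further.
- **That the trial is below its stated power.** This needs two-sided testing, which the article does not state; one-sided, 35 per arm gives the planned 80%.
- **That the large gains follow from the plan.** At 50%, the only spread that the plan gives, read as a CV, the gain is about three points. CVs of 100% and 150% are assumptions.

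It might also be said that covariates and transformation belong in a fuller document. But the article does state a definition and a test for its primary endpoint, and those can be judged as written.

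**Conclusion.** The point holds as one of efficiency. The stated primary analysis is valid, but it extracts less from the same samples than a baseline-adjusted log-scale analysis would under most of the conditions examined.

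How much less cannot be fixed from the article. On the raw scale, baseline adjustment is worth anything from nothing to 17 points of power, depending on r and on how the spread changes between t = 0 and t = 6. On log-normal assumptions, log-scale ANCOVA is worth about 3 points at CV 50% and about 15 at CV 100% or 150%. Those last figures assume a ratio of 0.70, placebo doubling and r = 0.5. The change is worth making because it costs little, not because the existing test would mislead.

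**What to change.** 1. Make the primary analysis an ANCOVA of log IL-6 at t = 6 on treatment and log IL-6 at t = 0. Report the ratio of geometric means with its 95% CI.
2. Optionally add time from trauma to incision as a covariate, if it is recorded. The article does not list it: Study protocol gives only a 12-hour window for the first sample. If the covariate is wanted, add the interval to the data collected.
3. Keep the t-test on raw Δ IL-6 as a sensitivity analysis.
4. In Sample size calculation, state one planning effect and the SD on the log scale, say whether the test is one-sided or two-sided, and recompute the number per arm.

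Cost: a change of wording, one or two degrees of freedom, and an effect reported as a ratio instead of a concentration difference. The t = 0 sample is already scheduled. Trial status reports no patients included, so at that stage the change could be made before any outcome data exist.

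### Kaplan-Meier, one of the two methods named for ARDS/MODS, does not estimate the stated presence-or-absence outcome; if death and discharge are censored it overstates the proportion affected

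*Protocol article*

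**What the plan says.** Under Statistical analysis, the article assigns the complications to time-to-event methods: "The occurrence of inflammatory complications, such as MODS and ARDS", it says, "will be examined with the use of a survival analysis, such as Kaplan Meier or Cox proportional Hazard".

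Under Outcome measurements, the secondary clinical outcome is "the effect of C1-INH on the presence or absence of ARDS or MODS and appearance of SIRS, sepsis or septic shock". The SIRS and SOFA scores used to judge these conditions "will be calculated on a daily base during hospitalization of the study subjects". The same section adds that intensive care stay, "duration of mechanical ventilation and total days of hospital admission are all recorded".

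The Objectives include "the effect of C1-INH on clinical outcome (e.g. ARDS, MODS, mortality, length of hospital stay"), so death and length of stay are outcomes in their own right and death is not part of the ARDS/MODS event. The Background says: "Presence of ARDS and MODS is a major risk factor for mortality, long time morbidity, a prolonged hospital stay".

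The article does not say how a patient who dies or is discharged before ARDS/MODS enters the analysis. It sets no fixed day for the outcome and names no competing-risk method.

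**The concern.** The stated outcome asks what share of patients get ARDS or MODS. Observation for it stops when a patient dies or leaves hospital. With Kaplan-Meier, the default is to censor such a patient, which amounts to assuming that he or she would later have developed the complication at the rate of those still admitted. That cannot be true of the dead, and it is implausible for patients well enough to go home. The curve then no longer estimates the share of patients affected.

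ARDS and MODS are the clinical consequences that the trial hopes eventually to prevent. An inflated absolute risk in either arm, or an inflated absolute difference, would mislead anyone using this trial to plan the next one. The treatment is also meant to be assessed for effects on death and length of stay, so departure from observation could differ between arms.

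**Working it through.** **Inputs.** From the article: the methods named, the presence-or-absence outcome, in-hospital scoring, and 35 patients per arm. The article gives no rate for ARDS/MODS, death or discharge, so there is no figure of its own to reproduce on this point. All rates below, and the 28-day window, are assumptions.

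**Formulas.** Take constant daily hazards h for the complication and d for death or discharge free of it, with T = 28 days.

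- 1-KM with death and discharge censored: 1 − exp(−hT)
- Cumulative incidence, the share actually affected: h/(h + d) × [1 − exp(−(h + d)T)]

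**Step 1, a simple case.**

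- h = 0.02, d = 0.05: 1-KM = 1 − exp(−0.56) = 42.9%. Cumulative incidence = (0.02/0.07) × [1 − exp(−1.96)] = 24.5%.
- h = 0.02, d = 0.08: 1-KM is again 42.9%. Cumulative incidence = (0.02/0.10) × [1 − exp(−2.8)] = 18.8%.

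**Step 2, size over a range.** Fix the true shares at day 28 and solve for the hazards. The total hazard H satisfies HT = −ln(1 − sum of shares), and h is its proportionate part.

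| True share affected | Censored | Assumed competing shares | 1-KM |
|---|---|---|---|
| 20% | deaths only | death 5–20% | 20.6–22.5% |
| 30% | deaths only | death 5–20% | 30.9–34.0% |
| 20% | deaths and discharges | death 5–15%, discharge 30–50% | 25.2–36.0% |
| 30% | deaths and discharges | death 5–15%, discharge 30–50% | 38.4–61.2% |

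Worked example for the lowest value in the last row: the shares sum to 0.30 + 0.05 + 0.30 = 0.65, so HT = −ln(0.35) = 1.050, hT = 1.050 × 0.30/0.65 = 0.485, and 1-KM = 1 − exp(−0.485) = 38.4%. At a true 30% the excess is therefore 0.9 to 4.0 points with deaths alone and 8.4 to 31.2 points with discharge added.

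**Step 3, comparison of arms.** Placebo shares at day 28: complication 30%, death 10%, discharge 40%. Placebo 1-KM is 45.3%.

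| Treatment effect assumed | Ratio, cumulative incidence | Ratio, 1-KM | Difference, cumulative incidence | Difference, 1-KM |
|---|---|---|---|---|
| None on any event | 1.00 | 1.00 | 0 | 0 |
| Complication hazard ratio 0.7 only | 0.75 | 0.76 | −7.5 points | −10.9 points |
| Hazard ratio 1, discharge 1.5 times faster | 0.87 | 1.00 | −4.0 points | 0 |
| Hazard ratio 0.7, discharge 1.5 times faster | 0.65 | 0.76 | −10.6 points | −10.9 points |

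When the competing hazards are equal, the ratio barely moves, but a real effect looks larger in absolute terms because both arms are inflated. The ratios separate once treatment changes discharge.

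**Step 4, false positives.** A log-rank test was simulated with 35 per arm and 4,000 runs per scenario, with no treatment effect on the complication hazard. It rejected in 4.5% to 5.9% of runs. The scenarios included a shared frailty linking complication, death and discharge, and treatment effects on discharge or death. The highest rate came with shared frailty and discharge twice as fast in one arm.

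**The case against.** The strongest reply is that the censoring rule is inferred. The article nowhere says that death or discharge will be censored, and it offers Kaplan-Meier and Cox as examples. Patients discharged event-free could be carried as event-free to a fixed day, and a fuller protocol or analysis plan may say so. That stands, and it is why the conclusion is conditional. It does not remove the point, because the article itself names a method that does not by default answer the question it sets. That is more than a detail left to another document.

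A second reply is that Cox is already offered. With competing events censored, it estimates a cause-specific hazard ratio, and the bias of 1-KM does not carry over to it. That also stands.

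A third is that Kaplan-Meier and cumulative incidence answer different questions. In Step 1 the complication hazard is the same in both cases, and 1-KM is the same too (42.9%); only the cumulative incidence moves. Under independent competing hazards, 1-KM therefore correctly shows that the complication hazard is unchanged. A reader might infer from the method named that the arm comparison must be biased. The documents do not support that: they give no effect on death or discharge, and the simulated false-positive rate stays near 5%.

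Finally, all the rates are assumed, and the large excess arises only if discharge is censored; deaths alone add little. This is correct, and the ranges are shown for that reason.

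**Conclusion.** The point holds in a limited form. The outcome is whether a patient gets ARDS/MODS in hospital, and Kaplan-Meier with death and discharge censored overstates that share. The overstatement is minor if only deaths are censored and can be large if discharges are censored as well; the figures rest on constant hazards and an assumed 28-day window.

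For the comparison of arms, the consequence is conditional. The ratio is distorted only if treatment changes death or discharge, or if these share unmeasured risk with the complication. With equal competing hazards, a null effect remains null, although a true effect is exaggerated on the absolute scale. It would go too far to say that the plan declares these events uninformative, or that the comparison is certainly wrong.

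This concerns a secondary outcome in a 70-patient trial sized on IL-6. It is worth correcting because the correction is cheap, but it does not threaten the trial's main result.

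**What to change.** For ARDS/MODS, replace Kaplan-Meier with the cumulative incidence to a fixed, pre-stated day, estimated by the Aalen-Johansen method with death and discharge alive as competing events. If every patient's status is known to that day or to an earlier death or discharge, this equals the simple proportion with in-hospital ARDS/MODS by that day, which may be reported instead. Compare arms by a risk difference with confidence interval. Keep Cox only as a cause-specific hazard ratio for the complication, shown beside the same models for death and for discharge. State in one sentence how patients who die or leave hospital event-free are counted.

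No new data are needed: the daily scores and days of admission are already collected, and mortality is already an outcome. There are two costs. Aalen-Johansen may need a routine outside the named software, though the simple proportion does not. And a cumulative incidence also reflects treatment effects on death and discharge: in Step 3, faster discharge alone lowered it from 30% to 26%. That is why the cause-specific models belong beside it.
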